### Statistical analysis

2.5

All the analyses are implemented with SPSS for Windows Version 19.0. And the data are represented by using proper features, for example, percentage, standard deviation as well as mean. Mann--Whitney *U* test and independent samples *t* test are utilized for comparison between the study and control groups. In order to compare the categorical variables between study and control group, we utilize the Chi-square test. For the significance level, the value of *P* needed to be less than .05.

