### Patients and randomization

2.2

This study includes 80 PU patients. A random number is assigned to all the patients through utilizing via using a random number table, and the allocation result is hidden in a random envelope. The patients are randomly divided into 2 groups, the control group and study group, with 40 members in each group. The patients meet the following criteria will be included. All participants meet the diagnostic criteria recommended via the National Pressure Ulcer Advisory Panel Society: complete skin defect, no bones, tendons and muscles exposure, no subcutaneous tunnel or scale; the patients selected are between 40 and 60 years old. The patients with the following criteria will be excluded: receiving other treatments that may influence the healing, for instance, radiation therapy and corticosteroids; patients with the complications of infection, malignant tumors, as well as peripheral vascular disease; and patients with serious diseases, containing kidney, cardiac, and liver diseases.

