### Observation indices

2.4

After 28 days, the state of the patients healing is observed closely, containing the dressing change frequency, curative effects, and the end-point efficiency. On the basis of the Pressure Ulcer Healing Scale ^[12]^ developed by the American pressure sore expert group, the quantitative scoring can be implemented, and therapeutic effects are assessed.

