## Results

3

The variables of clinical result among the groups are illustrated in the Table 1.

**Table 1 T1:** The clinical outcome variables between groups.

Variables	Study group (n = 40)	Control group (n = 40)	*P*
Branden scores			
Pretreatment			
Post-treatment			
Area of pressure sore			
Pretreatment			
post-treatment			
Frequency of dressing			
Average costs			
Wound complications			

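### The planned tests do not use the pretreatment values of sore area and Branden score; baseline-adjusted comparisons of these two outcomes would usually be more precise

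*Protocol article*

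**What the plan says.** Section 2.5 (Statistical analysis) states that the Mann-Whitney U test and independent-samples "test are utilized for comparison between the study and control groups". For categorical data it says: "In order to compare the categorical variables between study and control group, we utilize the Chi-square test". The P value "needed to be less than .05"; sidedness is not stated. No covariate, change score or adjusted model is named.

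Table 1 in section 3 (Results) is an empty shell with one P column for study versus control. Two of its five variables, "Branden scores" and "Area of pressure sore", have a pretreatment and a post-treatment row. Dressing frequency, average costs and wound complications have no pretreatment row.

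Section 2.2 randomises 80 patients, "with 40 members in each group". Section 2.4 begins "After 28 days, the state of the patients healing is observed closely" and then refers to quantitative scoring on a healing scale. It schedules no pretreatment healing score, and Table 1 has no row for that scale.

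**The concern.** Read together, section 2.5 and Table 1 describe one two-sample test at baseline and another after treatment. The starting value then plays no part in the treatment comparison. If a patient's starting area or score predicts the later value, two things follow:

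- Variation between patients that the baseline could explain stays in the error term, which costs power in a trial of 40 per arm.
- A chance difference between arms at the start passes, in proportion to the correlation, into the post-treatment difference. Section 2.2 sets no limit on ulcer size at entry and describes no stratification, so balance in starting area rests on chance.

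A P value in a pretreatment row does not help. After randomisation it tests only whether the allocation was random, and it says nothing about treatment.

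**Working it through.** The article gives no effect size, SD or power, so there is no figure of its own to reproduce.

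**Inputs from the article.** n = 40 per arm (section 2.2); alpha 0.05 (section 2.5).

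**Assumptions.** Two-sided testing; a true difference d = 0.5 SD; a correlation rho between pretreatment and post-treatment values of 0 to 0.7; normal data with a linear relation.

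**1. Chance baseline imbalance.** The standard error of the baseline difference is sqrt(2/40) = 0.224 SD. The probability that it exceeds 0.3 SD in either direction is 2 × [1 − Φ(0.3/0.224)] = 0.18.

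**2. Effect of an imbalance on the unadjusted test.** An imbalance b shifts the expected post-treatment difference by rho × b. For b = 0.3 this is 0.15 SD at rho 0.5 and 0.21 SD at rho 0.7. Write s = 0.224 and c = s × sqrt(1 − rho²). The type I error given b is Φ[(−1.96s − rho·b)/c] + 1 − Φ[(1.96s − rho·b)/c].

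| b (SD) | rho 0.5 | rho 0.7 |
|---|---|---|
| 0.2 | 4.3% | 3.1% |
| 0.3 | 6.9% | 7.6% |
| 0.4 | 11.0% | 16.1% |

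These are conditional rates. Averaged over all randomisations the error stays near 5%.

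**3. Power of the unadjusted t test.** Noncentrality is 0.5 × sqrt(40/2) = 2.236 on 78 df, giving 59.8%.

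**4. Power of ANCOVA.** The residual SD is multiplied by sqrt(1 − rho²). The variance is inflated by 1 + 1/(80 − 4) for estimating the slope, a factor of 1.0066 on the SD, and 77 df remain. Noncentrality is 2.236 / [1.0066 × sqrt(1 − rho²)].

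| rho | Noncentrality | ANCOVA power | Simulation: ANCOVA v t test | Equivalent n per arm, 40/(1 − rho²) |
|---|---|---|---|---|
| 0 | 2.22 | 59.2% | 57.8% v 58.3% | 40 |
| 0.3 | 2.33 | 63.3% | 65.0% v 61.8% | 44 |
| 0.5 | 2.57 | 71.7% | 71.9% v 60.4% | 53 |
| 0.7 | 3.11 | 86.7% | 87.1% v 58.8% | 78 |

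The simulation used 3,000 runs per setting. With no true difference, both methods rejected in 4.7% to 5.2% of runs. The last column ignores the small slope-estimation cost.

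**5. Break-even.** Setting the ANCOVA power equal to 59.8% gives rho = 0.115. At rho 0 the loss is 59.8 − 59.2 = 0.6 points.

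**6. Change scores.** A t test on change from baseline had simulated power of 33.0%, 46.7%, 61.1% and 82.7% at rho 0, 0.3, 0.5 and 0.7. That is below ANCOVA at every value.

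**The case against.** Several objections carry weight.

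- **Validity.** A reader might infer that the planned analysis is wrong. It is not: the unadjusted tests hold their error rate averaged over randomisations. The raised rates in step 2 of the working apply only given a sizeable imbalance.
- **Size of the gain.** Nothing in the article shows how strongly the starting value predicts the later one. Below a correlation of about 0.4 the gain is modest, and at zero there is a slight loss. The normal-model figures also do not carry over directly to sore area if many ulcers have healed to zero.
- **Scope.** A reader might extend the point to every outcome, or to the healing scale in particular. Only sore area and the Branden score have a documented baseline.
- **Two tests for one comparison.** Section 2.5 lists the t and Mann-Whitney tests with no rule for choosing. Reporting whichever P value is smaller would raise the error to about 6% (normal data) or 7% (lognormal data) in a 20,000-run simulation. The article does not say that anyone will do this, and a choice rule may sit in an unseen analysis plan, so no inflation is claimed here.
- **Inference from layout.** That the tests use raw post-treatment values, and that the pretreatment rows get a P value, is read from an empty table; section 2.5 does not say so. Even if change were tested instead, ANCOVA did better in the simulation.
- **Detail left to a fuller plan.** The article names its tests and shows its results table, so this is a stated choice and not an omission.

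What survives is an efficiency point confined to two outcomes.

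**Conclusion.** The point holds in a limited form. For sore area and the Branden score, the stated tests and table leave a collected baseline out of the treatment comparison. With 40 per arm and an assumed 0.5 SD effect, adjustment changes power from about 60% to between about 59% (correlation 0) and 87% (correlation 0.7). It gains whenever the correlation exceeds about 0.12. It also removes the linear effect of chance imbalance in the adjusted baseline, and only that. The effect size, the correlation and normality are assumptions. The amendment is worth making, but the planned analysis is not invalid without it.

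**What to change.** In section 2.5, add:

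- Post-treatment sore area and Branden score are each compared by ANCOVA, with treatment as factor and the pretreatment value as covariate, reporting the adjusted difference and its 95% CI.
- For sore area, use a rank-based ANCOVA, or a transformation defined at zero such as log(x + c) or the square root, because healed ulcers have zero area.
- Treat the healing-scale score in the same way only if a pretreatment score is recorded.

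Keep the existing two-sample and Chi-square tests for outcomes without a baseline (dressing frequency, costs, complications), so that none is left without a stated test. In Table 1, keep the pretreatment summaries but drop their P values.

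For sore area and the Branden score this needs no extra patients, visits or data. It costs a few lines of text and one degree of freedom, about 0.6 points of power if the correlation is zero.

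### No outcome is named primary, all are tested at an unadjusted P<.05, and the outcomes in section 2.4 and Table 1 overlap only on dressing frequency

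*Protocol article*

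**What the plan says.** Outcomes appear in two places in the protocol article.

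- **Section 2.4 (Observation indices)** describes the assessment after 28 days as "containing the dressing change frequency, curative effects, and the end-point efficiency". It then says that, using the Pressure Ulcer Healing Scale, "the quantitative scoring can be implemented, and therapeutic effects are assessed".
- **Section 3 (Results)** says: "The variables of clinical result among the groups are illustrated in the Table 1". That table, captioned "The clinical outcome variables between groups", has a P column. Its rows are Braden score and ulcer area (each before and after treatment), dressing frequency, average costs and wound complications.

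Neither place, nor the abstract, calls any outcome primary.

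Section 2.5 states the tests: "Mann--Whitney *U* test and independent samples *t* test are utilized for comparison between the study and control groups", and "In order to compare the categorical variables between study and control group, we utilize the Chi-square test". It then sets a single criterion, that P "needed to be less than .05". It does not give an order of testing, an adjustment, or a rule for concluding that the intervention works. The stated objective is effectiveness in general, and the anticipated conclusion concerns healing efficiency. Neither is tied to a named outcome.

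**The concern.** With no primary outcome and one threshold for everything, the 5% level protects each test separately but not the trial's overall conclusion. Because the objective is general, a small P on any of several outcomes could be put forward as support, and the headline outcome could be chosen after the results are known.

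The mismatch between the two lists makes this worse. The instrument that section 2.4 uses to judge therapeutic effect is absent from the results table. Ulcer area has a results row but is not mentioned in section 2.4. A reader cannot tell from the article which measure of healing the trial is meant to be judged on.

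**Working it through.** **The plan's own figure.** The only figure is the per-test level of .05. The article states no error rate across outcomes, so there is none to reproduce.

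**Step 1. Compare the two lists.**

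| Outcome | Section 2.4 | Table 1 |
|---|---|---|
| Dressing frequency | yes | yes |
| Curative effects | yes | no |
| End-point efficiency | yes | no |
| Healing-scale score | yes | no |
| Braden score | no | yes |
| Ulcer area | no | yes |
| Average costs | no | yes |
| Wound complications | no | yes |

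Table 1 alone gives k = 5 post-treatment outcomes; its two pretreatment rows are not outcome tests. Adding the three items found only in section 2.4 gives k = 5 + 3 = 8. If those three are really one outcome, k = 5 + 1 = 6.

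**Step 2. Inputs.** The level is .05 per test (section 2.5). Sidedness is not stated, so two-sided testing is assumed. Correlations between outcomes are not given, so a range is assumed.

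**Step 3. Independent outcomes, no true difference on any.**

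- At least one P<.05 in either direction: 1 − 0.95^k.
  - k = 5: 1 − 0.7738 = 22.6%.
  - k = 6: 26.5%.
  - k = 8: 1 − 0.6634 = 33.7%.
- At least one P<.05 favouring the study arm (.025 per test): 1 − 0.975^k.
  - k = 5: 11.9%.
  - k = 8: 18.3%.
  - A single outcome: 2.5%.

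**Step 4. Correlated outcomes.** Test statistics were simulated as normal variables with a common correlation (1,000,000 draws, two-sided critical value 1.96).

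| Assumed correlation | k = 5, either direction | k = 8, either direction | k = 5, favouring study arm | k = 8, favouring study arm |
|---|---|---|---|---|
| 0.3 | 20.9% | 30.0% | 10.5% | 15.2% |
| 0.5 | 18.3% | 25.1% | 9.1% | 12.6% |
| 0.8 | 12.7% | 15.8% | 6.4% | 7.9% |

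**Step 5. A narrower count.** Setting aside average costs and dressing frequency as not clearly measures of efficacy leaves three Table 1 outcomes. Under independence, k = 3 gives 14.3% in either direction and 7.3% favouring the study arm.

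Every scenario exceeds the single-test rate (5%, or 2.5% in one direction). How far it does so depends on the count and the correlation.

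**The case against.** **Scope.** Adjustment for multiplicity and the ranking of secondary outcomes are commonly left to an analysis plan or a full protocol, and neither is shown. That stands: the absence of an adjustment method would not be a finding by itself. But the choice of primary outcome is a protocol-level decision. The article has a section on outcomes, a section on analysis and a results table, and what they fix is two unranked lists that disagree.

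**The count.** Eight is probably too many. Section 2.4 can be read as making the healing scale the instrument for curative effects, and end-point efficiency is undefined and may come from the same score. Average costs is not an efficacy measure. This stands, so 34% is a ceiling.

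**Correlation.** Area, healing score, curative effects and efficiency describe the same wound and may be strongly correlated, which lowers the rates. This also stands, although the article gives no value.

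**The success rule.** A reader might infer that the plan treats any one significant outcome as proof of effectiveness. It does not say so; section 2.5 states only a significance level. What can be said is that no other rule is given.

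**Dressing frequency.** A reader might also infer that false positives are even more likely because dressing changes follow protocol rules. The article does not support this. A difference produced by the protocol would be a real difference, not a false positive. Section 2.3 also gives one to two days both for the control dressing and for sponge replacement, so a built-in difference is not shown.

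**Conclusion.** The point holds and should be corrected. No primary outcome is named, one unadjusted threshold covers all comparisons, and the two outcome lists share only one item.

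If no outcome truly differs, the chance of at least one P<.05 in either direction is 23% for five independent Table 1 outcomes, about 13–18% at assumed correlations of 0.8–0.5, and at most 34% with eight independent outcomes. The single-test figure is 5%.

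It is tempting to read 23–34% as the chance of falsely claiming that the intervention works. It is not, because it includes differences favouring control. The chance of a false result favouring the study arm is about 12–18% under independence, against 2.5% for one outcome, and it is lower with correlation.

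These figures assume two-sided tests, a count of five to eight outcomes, and correlations that the article does not give. The open choice of headline outcome does not depend on any of these assumptions.

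**What to change.** In sections 2.4 and 2.5, before outcomes are compared by group, name one primary healing outcome at day 28, tested at two-sided .05. State that the conclusion on effectiveness rests on that test alone. Two candidates fit the article, and the choice is the sponsor's:

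- **Pressure Ulcer Healing Scale score.** Section 2.4 already ties it to therapeutic effect. It needs a row in Table 1. No baseline score is mentioned, so analyse change or adjust for baseline only if one is collected; otherwise compare day-28 scores.
- **Ulcer area, adjusted for its pretreatment value.** Table 1 already has both rows. It needs adding to section 2.4.

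Make the two lists agree, and say whether curative effects, end-point efficiency and the healing scale are one outcome or several.

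Report all other outcomes as secondary or exploratory with 95% confidence intervals, or Holm-adjust them across the number actually tested. The smallest P must then be below .05/4 = .0125 for four, .05/5 = .01 for five, or .05/7 = .0071 for seven.

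**Cost.** This takes a few sentences and a table row, plus a baseline healing-scale assessment if change in that score is wanted. The other P values lose confirmatory status. Splitting the level across outcomes instead would cost power. With 40 per arm, the difference detectable with 80% power is (z for the level + 0.842) × √(2/40): 0.63 SD at .05, 0.76 SD at .01 (five outcomes) and 0.80 SD at .00625 (eight outcomes). A single primary outcome avoids that loss.

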## Results

3

The variables of clinical result among the groups are illustrated in the Table 1.

**Table 1 T1:** The clinical outcome variables between groups.

Variables	Study group (n = 40)	Control group (n = 40)	*P*
Branden scores			
Pretreatment			
Post-treatment			
Area of pressure sore			
Pretreatment			
post-treatment			
Frequency of dressing			
Average costs			
Wound complications			

## Discussion

4

PU risk areas are usually regarded to appear in anatomical positions with almost no soft tissue coverage on the bone protrusions.^[13,14]^ In these areas, smallest tissue coverage does not allow the appropriate absorption and the pressure redistribution, thus they are sensitive to the pressure sores and ischemia. Patella, greater trochanter, calcaneus, ischial tubercle, and lateral malleolus are the high-risk anatomical areas for PU in the patients.^[15]^

Conventional cleaning, disinfection as well as some other generally utilized medical gauze, cannot be degraded in the vivo, and prescription includes light powder, which is toxic to kidney and liver.^[16]^ Tissue fluid can be effectively absorb by the gelatin sponge. The gelatin sponge can promote the platelet rupture, and release a large number of the coagulation factors, thereby promoting the coagulation of blood. Furthermore, the gelatin sponge can support the blood block for the prevention of the blood block from decreasing, leading to anastasis. And it is also a kind of excellent drug carrier. Published studies have indicated that it can promote the healing of wound in comparison with gauze or the traditional Chinese medicine.^[17]^ Our study program can offer a strong basis for nursing intervention of gelatin sponge combined with the moist wound-healing in treating the PU.

## Conclusion

5

The nursing intervention of gelatin sponge combined with the moist wound healing may evidently increase the healing efficiency of PU.
